## Abstract

*Background*: Childhood obesity is a critical health issue, both currently and for the foreseeable future. To prevent obesity, behavior changes are essential. Smartphones can be a good tool, as the number of child smartphone users is rapidly increasing. We have developed a mobile platform system named “HAPPY ME,” which is a smartphone application coupled with a wearable device, designed to improve healthy behaviors to prevent childhood obesity. This study aimed to evaluate the effectiveness of obesity prevention among children 10–12 years of age using HAPPY ME. *Methods*: A total of 1000 participants, all fifth and sixth graders from four schools, were assigned to either control or intervention groups by school. Students in the intervention group used HAPPY ME. The study comprises a safety test, a 12-week efficacy test, and a six-month follow-up test to determine the long-term effects of preventive intervention via the integrated service platform. The integrated service platform aims to facilitate child-parent-school participation, involving the child-parent mobile application, a child-teacher mobile web, and a school website. Primary outcome measures are behavioral changes, including healthy eating, increased physical activity, and fitness. Secondary outcome measures are changes in anthropometric parameters (body weight, height, body mass index z-score, and waist circumference), body mass index (BMI) percentiles (obesity rate), and psychological perceptions among participants. *Conclusions*: The results of this study will offer evidence of the effectiveness of a mobile platform service with a multi-component intervention program based on a comprehensive approach.

## 1. Introduction

The rate of childhood obesity in Korea is constantly increasing, with 26.4% of boys categorized as either overweight or obese as of 2013, exceeding the Organization for Economic Cooperation and Development (OCED) average of 24.3% [1,2]. Showing the disparity between males and females in terms of childhood obesity [2], 14.1% of girls are categorized as being in the same condition. According to the measure of BMI for children and teens by the Centers for Disease Control and Prevention (CDC), childhood obesity is defined as a BMI at or above the 95th percentile for children of the same age and sex, whereas overweight is defined as a BMI at or above the 85th percentile and below the 95th percentile for children of the same age and sex [3]. Childhood obesity can seriously impact public health matters, not only causing enormous medical expenses, but also resulting in various illnesses over the lifetime [4,5]. For these reasons, numerous studies have focused on childhood obesity prevention and management intervention [6,7,8,9,10]. Also, research on childhood obesity has highlighted the necessity of combined dietary-behavioral-physical activity intervention along with family-based education to foster a supportive home environment, which is integrated with a child’s school system [11,12,13,14,15,16]. School-based approaches have been shown to be the most effective in solving the health problems of school-age children, including obesity [13,17,18,19]. Recent studies have introduced new technologies to help prevent or manage obesity, using smartphone applications that tackle issues of dietary and physical activity (PA), together with wearable devices that track the intensity of the user’s PA as well as daily and weekly calorie consumption [20,21,22,23,24,25,26]. Insofar as behavior changes are essential for the prevention and treatment of obesity [27], mobile health (mHealth)—a general term that refers to the use of mobile phones and other wireless technology in medical care—can be a useful tool in implementing and monitoring behavior changes [28]. Types of intervention that involve smartphone-assisted programs have been shown to be effective in obese adolescents [29]. Evidence is lacking, however, as to whether these types of intervention programs are well suited for school-age children. Regardless, mobile applications targeting children to promote healthier behaviors have potential, because many youth begin interacting with computers and cell phones at very early ages [30]. Thus, smartphones, if used in childhood obesity intervention programs, will be familiar tools for children. According to the Korea Information Society Development Institute as of 2015, 72.3% of upper-grade elementary school students have their own cellular phones. Among these, 59.3% have smartphones [31]. In the findings of our first pilot study, smartphones were owned by 55.2% (boys, 49.5% and girls, 60.8%) of school-age children in grades four through six. Accordingly, we assumed that our approach to the problem of childhood obesity with smartphones is plausible. It has been stated in previous studies that large-scale data for childhood obesity prevention with smartphones are lacking [12,32]. This trial will be the first to assess childhood obesity prevention in a school setting (also including parents) with a multi-component program using a mobile platform system called HAPPY ME, operated via a smartphone application and a wearable device. Our goal with this ongoing trial is to evaluate the effectiveness of childhood obesity prevention with the HAPPY ME platform for students, parents, and teachers.

## 2. Methods

### 2.1. Study Participants

Participating schools were recruited by a sanctioned announcement involving official letters from the Metropolitan and Provincial Offices of Education in Gyeonggi Province. Since the recruitment publicity included information regarding the use of mHealth to tackle childhood obesity, the study could not be masked and all applicant schools wished to be designated as intervention schools. We took pragmatic approach to intervention and control group allocation due to the fact schools were unwilling to be randomized. According to our pilot study conducted the previous year, less than 40% of students in fourth grade have smartphones, which can lead to a serious selection bias. The pilot study showed that the number of students who own smartphones increases as students advance through grades at school. Therefore, we determined that fifth and sixth graders were eligible to participate in our research by following a nine-month-long study using smartphones and wearable devices for the prevention of childhood obesity. The sample size was determined based on the government funding, the feasibility of the study, the number of measurements per participant, the number of students we could recruit, and the potential dropout rate considering the age of participants rather than the effect sizes of the intervention. We chose 250 students from each school as an appropriate number, for a total of 1000 students across four participating schools. To categorize children’s weight status, we used the standard growth chart for infants and children by the Korea Centers for Disease Control and Prevention [33]. Written consent was collected from all participating children and their parents. Inclusion criteria were fifth-sixth graders (10–12 years old), no previous diagnosis of systemic or metabolic diseases, and Android smartphone users with parental consent, students who did not refuse to participate (see Figure 1). Finally, 288 students were assigned to a control group, and 558 students were allocated in the intervention group. Any physical restrictions in participants were assessed during meetings with teachers and in loading the program to the smartphone applications of participants.

#### 2.1.1. Control Group

Students in the control group underwent the same measurements as students in the intervention group, including Physical Activity Promotion System (PAPS) measurements and lifestyle questionnaires administered at the baseline, at week 12, and at month 6. Comprehensive assessments of dietary habits, physical activities, and psychological variables are planned for each assessment period using questionnaires. The control group received the same two group education sessions. Data for these 250 students from one elementary school were collected.

#### 2.1.2. Intervention Group

##### HAPPY ME Platform

In this trial, we developed the HAPPY ME platform, which involves parents and teachers in monitoring and providing an encouraging environment for participating children. The platform serves as a data reservoir for teachers, enabling them to track students’ eating behaviors, screen time, and anthropometric parameters. Data are shown in numbers and graphs and allow teachers to support the children with encouraging messages. In addition, educational materials on healthy eating habits and exercise are included in the platform content. This information is featured as guidelines for teachers and parents. The platform delivers feedback messages to children and parents. The application logic for the selection of feedback for the HAPPY ME platform for parents and children differs according to the differing needs of participants in this study. The platform sends PAPS data and performance data from the applications of students to a mobile web for teachers.

##### Intervention for Children

Among 750 students from the three intervention schools, students who met inclusion criteria for this study downloaded the “HAPPY ME for students” application. Due to financial and time limits of the developer, the application was developed for Android systems only. This application serves as a self-monitoring tool that focuses on factors known to be associated with childhood obesity including dietary habits, screen time, sleep duration (measured in hours), and physical activity [16,24,25,34,35,36,37,38]. As previously described, HAPPY ME facilitates healthy behavior decisions using gamification and self-monitoring strategies [38,39]. The application sends tailored messages to children to encourage them to complete daily quests for physical activities and to practice healthy dietary habits, such as eating breakfast, choosing fruits and vegetables, and avoiding sugar-sweetened beverages and fast foods, all of which are helpful habits in preventing childhood obesity. The application collects information about participants’ dietary habits and physical performance to categorize and offer optimal feedback to achieve behavioral changes to prevent obesity. Herein, the participating students recorded basic information including weight, height, dietary behavior, and number of hours of sleep at the beginning of the application. Students used height information measured by PAPS at the beginning of the study. Input data in the application automatically categorized the individual status of each student into six categories of dietary behavior and three categories of fitness within the application. For dietary behavior, we defined the following six categories as standard and optimal goals for healthy diets in children: consumption of vegetables five times per day, consumption of fruits twice a day, drinking water instead of sugar-sweetened beverages (SSBs), eating a healthy meal instead of fast or instant food, not eating snacks, and not eating late at night. For physical performance, we defined the following three categories to measure the proper amount of walking per day according to sex: high activity, moderate activity, and low activity. The high activity category includes activities with a number of counted steps over 14,000 steps for boys and over 12,000 steps for girls. Moderate activities are defined as 7000–14,000 steps for boys and 6000–12,000 steps for girls, and low activities are measured as under 7000 steps for boys and under 6000 steps for girls [40]. Once the individual is categorized according to behavior, the application presents a dietary and physical activity quest to encourage users to practice better health behaviors to prevent obesity. Students choose one challenge among the quests presented, and the mission lasts for one week. A tailored message is offered once a day to users based on their performance of the selected quest. After one week, children may choose another quest or continue the previous quest if the quest has not been successfully completed. Eventually, students complete all of the quests according to the guidelines of the application. Participants can monitor their daily and weekly performances, and the application provides feedback and socio-emotionally supportive messages according to user behaviors. These messages are generated from a message pool that the research team developed under a trans-theoretical model. Messages are automatically sent to students according to the logics of each performance. To add a gamification element to the application, children get points if they have completed daily quests, which in turn leads to a higher level of fitness and a healthier diet. Teachers and parents are able to assess how well individuals are doing by comparing these scores among classmates through the application as a series of gamifying elements and, accordingly, to better motivate students to complete the quests assigned to them. If the children do not wish to compare the scores with classmates, they have an option in the application not to be compared. Participants in the intervention group also received an activity tracker called the Walkie + D Coffee (Green Cross Healthcare Inc., Seoul, Korea) via the research team at each school. According to tracker accuracy tests conducted by our developers, the accuracy between volume of oxygen uptake (VO2) and calorie expenditure (kcal/min) through gas analysis and the expenditures of calories according to step count by the device was 80% [41]. Therefore, we considered this device to be a usable activity tracker. Students were instructed to wear the device on their wrist. Daily, weekly, and monthly physical activity data, such as intensity of workouts, step count, and number of calories expended by walking or running with the Walkie + D Coffee, are transferred via Bluetooth to the participant’s smartphone.

##### Intervention for Parents

Parents downloaded the “HAPPY ME for parents” application to receive feedback from the platform and to monitor their child’s dietary habits and physical activity. The main role of parents in this study is to provide their children with an optimal environment to improve healthy behaviors. Educational materials about obesity, such as risks of obesity, healthy eating habits, and nutrition, are included for reference if necessary. As the main food preparers and emotional supporters of the participants, parents receive tailored messages once a week in the context of the child’s performance to encourage them on their weekly missions. The tailored messages for parents also offer guidance on how to create a healthier home environment.

##### Intervention for Teachers

The main role of teachers in this prevention-based intervention program is to encourage students to improve healthy behaviors rather than to monitor participants’ performance (which is optional). The scope and content for the teacher websites at the schools comprising the intervention group (“HAPPY ME for teachers”) were created according to teacher opinions based on focus-group interviews and a need assessment survey. The primary teacher opinion was to minimize extra work on the part of teachers for this program to guarantee feasibility of the program in the real school system. Teachers are very busy with their original duties. It is important to reduce the burden on teachers and to support their original educational duties. We asked teachers in charge of classes with participating students to encourage healthy behaviors among their students at least once a week. The website is open for all teachers at participating schools. The content of the website comprises teacher-friendly educational material about nutrition and physical activity, test results of physical fitness measures among participants, and monitoring capabilities regarding application data on participating students from their classes. The educational materials contain information to enhance the performance of key quests in the application. Teachers may use the educational materials during lessons to better help students in following the HAPPY ME quests during the 12-week efficacy test period. The materials provided on the teacher websites are modified to be more appropriate for teaching a health-related curriculum. Teachers in charge of classes with participating students can encourage participants (or the whole class) using a bulletin or sending messages via the website, which can then be shown in an individual’s smartphone application.

### 2.2. Study Design

The current study is a school-based nonrandomized controlled trial funded by a national grant to prevent childhood obesity in Korea, which has been undertaken utilizing a safety test, a 12-week efficacy test, and a planned subsequent six-month follow-up test for long-term effects. During the study period of 37 weeks, participating students are expected to use their smartphones along with a wearable device, while parents and teachers will receive feedback messages about the performance of participants via smartphones and teacher websites. Data is collected on the part of the research team by monitoring the HAPPY ME platform and spot feedback from teachers and children. For the feedback session with children, our research team will be assigned to each school for three months. A group meeting with parents and teachers for feedback is planned to occur during the three-month efficacy trial. To evaluate the students’ physical performance, data collected by the Physical Activity Promotion System (PAPS) from each school will be monitored. Reporting PAPS data is mandatory in the Korean school system. The PAPS consists of tests to assess cardiac endurance, muscle strength, power, flexibility, and body composition. The PAPS was developed by the Korean government according to public interest in health concerning the growing number of obese and/or weak children. Every elementary school performs PAPS testing once or twice a year to measure student health and, based on results, offers individual exercise prescriptions to every participant. For the schools participating in the application efficacy trial herein, participating students will perform PAPS testing before and after the trial under the guidance of experienced examiners to test the participants’ overall physical fitness, including obesity evaluation, by measuring percent body fat using bioelectrical impedance analysis (BIA). A lifestyle questionnaire which was designed and internally validated was conducted at the beginning of the trial. The questionnaire will also be conducted at week 12 and at the end of the trial. The questionnaire consists of behavioral factors regarding sleep, stress, dietary habits, and activity habits, as well as the amount of screen time by participating children and psychological factors, such as body image. Every participant is required to attend two group education sessions at their respective schools featuring information on a healthy diet and food additives, as well as easy-to-learn physical activities from professionals at week 0 and at week 8 during the 12-week efficacy test period (see Table 1).

#### 2.2.1. Phase 1: Safety Test

Participants in the intervention group downloaded an application called What’s UBhind? (Rinasoft Inc., Busan, Korea) to test the safety of the intervention program one week before baseline. The application provides daily, weekly, and monthly reviews of the amount of screen time involving a user’s smartphone, thereby enabling the user to accurately depict his or her smartphone screen time (ST). It is known that excessive ST is related to lower self-esteem, depression, and increased odds of obesity or being overweight. Accordingly, monitoring screen time is crucial to some obesity prevention intervention studies [16,24]. To assess ST, individuals can customize limits in the application, which will alert users as soon as the set screen time has been exceeded. Screen time is reported to the HAPPY ME websites of teachers. According to an algorithm we have developed, feedback messages on excessive screen time will be sent to both children and parents. Data as to whether this intervention involving smartphones impacts the rising amount of screen time among children will be collected and monitored by the research team. The safety test will continue until the six-month follow-up period is finished, but it is not mandatory.

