## Figures and Tables

**Figure 1 ijerph-14-00184-f001:**
[figure not shown]
Flow chart of the study.

**Table 1 ijerph-14-00184-t001:** Timeline of the study protocol procedure.

Study Procedure	Safety Test	Efficacy Test				Long-Term Effect Test
	A Week before	Baseline	Week 4	Week 8	Week 12	Month 6
1. Workshop for intervention group	I	I				
2. Screen-time monitoring	I	I	I	I	I	
3. Group education session		I, C		I, C		
4. Lifestyle questionnaire		I, C			I, C	I, C
5. PAPS measurement		I, C			I, C	I, C

I: Intervention group, C: Control group.

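### The safety test rests on a screen-time app used only in the intervention group; questionnaire screen time, collected in both groups, is not assigned to it

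*Protocol article*

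**What the plan says.** Section 2.2.1 of the protocol article describes Phase 1. The instrument is a commercial screen-time app, and its users are one group: "Participants in the intervention group downloaded an application called" it, "to test the safety of the intervention program one week before baseline". The question put to the data is causal: "Data as to whether this intervention involving smartphones impacts the rising amount of screen time among children will be collected".

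The same section gives the app an active role. It says "individuals can customize limits in the application, which will alert users as soon as the set screen time has been exceeded", and that "feedback messages on excessive screen time will be sent to both children and parents". Screen time is also passed to the teachers' site.

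On duration it says: "The safety test will continue until the six-month follow-up period is finished, but it is not mandatory".

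In Table 1 the row "Screen-time monitoring" is marked for the intervention group only, and its month 6 cell is blank.

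Section 2.2 lists the contents of the lifestyle questionnaire, which include behavioural factors "as well as the amount of screen time by participating children". Section 2.1.1 and Table 1 give this questionnaire to both groups at baseline, week 12 and month 6. Section 2.2.1 does not mention it.

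**The concern.** The question is whether the program changes children's screen time. An answer needs an estimate of what screen time would have been without the program. The named instrument has no control data, so its change over time mixes any program effect with whatever else alters screen time over the school year. The instrument also prompts children to cut down, so a level or falling trace could come from the prompts, and a rising one could come from age or season.

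At stake is the one safety question the article sets. If it is reported from the app alone, either reassurance or alarm would be unsupported. The trial has a control group and a screen-time item that both groups answer, so this is avoidable.

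**Working it through.** The article gives no screen-time mean, standard deviation, trend or target difference, so there is no figure to reproduce. The check compares the two instruments and asks what each can estimate.

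| | Monitoring app (2.2.1, Table 1) | Lifestyle questionnaire (2.1.1, 2.2, Table 1) |
|---|---|---|
| Intervention group | 5 marked cells: a week before, baseline, weeks 4, 8, 12 | 3: baseline, week 12, month 6 |
| Control group | 0 marked cells | 3: baseline, week 12, month 6 |
| What it records | smartphone screen time | amount of screen time, device not stated |
| Acts on the child | yes: alerts and feedback | none described |

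**What the app can estimate.** Write P for the effect of the rest of the program, A for the effect of alerts and feedback, and T for change that would have happened anyway.

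- App change in the intervention group = P + A + T.
- This is one observed quantity with three unknowns. With no control value for T, neither P nor P + A can be recovered. Any T enters the estimate in full.

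**What the questionnaire can estimate.** Write R for any shift in reporting, and T_I and T_C for background change in the two groups.

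- Intervention change = P + A + T_I + R_I.
- Control change = T_C + R_C.
- Difference = (P + A) + (T_I − T_C) + (R_I − R_C).

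The target is now P + A, the effect of the whole package including its feedback. Background change shared by the groups cancels. Two errors remain: a different background trend in the single control school, and different reporting because only one group receives screen-time feedback.

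**Effect of the early installation.** The intervention group has the app one week before baseline. Suppose this shifts its reported baseline by a. With baseline slope b, the adjusted difference is (Y_I − Y_C) − b(X_I − X_C), where Y and X are group means at follow-up and baseline. It therefore moves by −b·a. If the alerts had already lowered reported screen time (a negative) and b is positive, the adjusted difference is too high by b·|a|, so the package looks less favourable than it is. The document gives neither a nor b.

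**Children available.** Section 2.1 gives 288 controls and 558 intervention children: 288 + 558 = 846. Section 2.1.1 speaks of 250 children in the control school; on that figure the total is 250 + 558 = 808. Both are ceilings before any loss. The app supplies 0 controls under either figure.

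**Duration.** The text of section 2.2.1 carries monitoring to the end of follow-up, while the last mark in Table 1 is at week 12.

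**The case against.** The strongest reply is that the stated data do include a controlled measure. The questionnaire covers screen time in both groups, section 2.4 provides general between-group methods, and nothing forbids applying them. Nor does section 2.2.1 specify a single-group before-and-after test; it says the data will be collected and monitored. Linking an instrument to an analysis can be left to a fuller document. This stands to the extent that a reader who inferred that the safety question cannot be answered at all would go beyond the text. It does not remove the point. Section 2.2.1 and Table 1 do fix the instrument, the group and the timing of the safety test, and no later analysis can create app data for controls.

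Other stronger readings are also unsupported:

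- The word *rising* might be taken as the plan admitting a background trend. It may equally mean a rise caused by the program. The argument needs neither reading, since an uncontrolled change cannot be attributed.
- A reader might infer that heavy users will leave the data because use is voluntary. The remark on voluntary use sits in the sentence about continuing through follow-up and may apply only there. Selective loss is possible, but nothing shows it will occur.
- The alerts and feedback might be called a mask over real harm. If they belong to the delivered package, their effect is a legitimate part of the safety target, and the alert limits are set by the users themselves. What stands is that the app data cannot separate this effect from the rest or from background change.
- The blank month 6 cell could mean optional passive monitoring with no scheduled procedure. The table does not say so, and clarifying it is enough.

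**Conclusion.** The point holds in a limited form. As section 2.2.1 and Table 1 stand, the safety test yields an uncontrolled change in one group, measured by a tool that also acts on screen time, and this alone cannot show whether the program affects screen time. A better comparison is already being collected but has not been assigned to the question. This is an inexpensive improvement, and the trial does not lack controlled data.

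The size is structural: no controls have app data, against up to 846 children (808 on the other control figure) with questionnaire data at three times. How far the app-only answer could be wrong in hours is unknown, because the document gives no trend.

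The conclusion assumes that the screen-time item is asked in the same form in both groups and at each assessment, as the shared questionnaire implies. The controlled comparison is better but not clean. With one control school and no randomisation (sections 2.1.1 and 2.2), it stays confounded with school.

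**What to change.** In section 2.2.1:

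1. Name the between-group difference in questionnaire screen time at week 12 and at month 6, adjusted for baseline screen time, as the controlled safety comparison.
2. Report the app data as a description of the intervention group only, with the proportion of children still providing data at each time.
3. State the limits: screen time is self-reported, and reporting may be affected by feedback that only the intervention group receives; the questionnaire may cover more than smartphone use, so it complements the app and does not replace it; the intervention group's baseline is taken one week after the app was installed; and there is one non-randomised control school, so the result remains confounded with school.
4. Reconcile the text, which continues monitoring to the end of follow-up, with Table 1, which has no screen-time entry at month 6.

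Write the safety model out rather than borrowing the regression in section 2.4. That model lists baseline BMI z-score but not the baseline value of the outcome. It also includes school; because school determines group here, school entered as a fixed factor would leave no separate group effect to estimate.

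The cost is a change of wording in section 2.2.1 and Table 1 plus one further analysis. No new data are needed. The price is that the controlled safety result depends on self-report.
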